**Methods:**

*Design*: A mixed-methods design will be used, based upon the RE-AIM framework (see <http://www.re-aim.hnfe.vt.edu/>). Objective 1 (Reach) will refer to a pre-existing dataset from a random cross-sectional population-level household survey previously conducted by MSF for separate purposes; routine cohort data from two MSF clinics in Irbid; and qualitative data from focus groups, semi-structured and key informant interviews. Objective 2 (Effectiveness) will use a cohort study design of chronic disease patients at the MSF-run clinics in Irbid. It will use routine clinic data to explore trends in clinical outcomes and other quality of care indicators, which occurred during MSF’s implementation of this NCD care model in Irbid. It will also include descriptive analysis of total and unit programmatic costs. Objective 3 (Adoption/acceptance) will use qualitative data to explore issues around adoption and acceptance of the model components through participant observation, focus group discussions and semi-structured interviews with patients, staff and key stakeholders. A small exploratory study to develop and test a short survey of self-reported medication adherence and beliefs will also be undertaken. Objective 4 (Implementation) will use routine cohort data, clinical audit, participant observation, routine costing data and qualitative data (as described above). Objective 5 (Maintenance) uses routine cohort data, qualitative data (as described above) and data on medical supplies, costs and staff time estimates.

*Study participants:* The pre-existing cross-sectional health service access survey included Syrian refugees households living outside of camp settings in Irbid governorate, selected using a two-stage cluster design. For the routine cohort data, all patients six years and older with confirmed NCDs attending the two MSF clinics in Irbid more than once, will be included (using patient records from January 2015 to December 2016). For the qualitative research, respondents will be purposively selected patients and/or health workers, past and present, from the two MSF clinics in Irbid. Key stakeholder interviews will include staff from MSF and other NGOs, Jordanian MoH staff and community leaders. For the medication adherence survey, a random sample of 300 consenting service users attending the MSF clinic will be selected.

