**Table 1. Standard epidemiological and quality indicators for MSF NCD services**

### 1.1.4 Evolution of model of care

| **Epidemiological / service activity indicators** | **Quality indicators** |
| --- | --- |
| Number / % of new patient consultations per month | Number / % of DM patients that have micro-albuminuria or urinary protein testing in the last year (Target = 80%) |
| Number / % of follow-up consultations per month (% of total visits) (by age, gender, nationality) | Number / % of patients with DM or on ACE inhibitor (ACEi) with Creatinine testing in last year (Target 80%) |
| Number/ % of patients presenting with the following morbidities: DM Type I, DM Type II, Hypertension,  other CVD, Asthma, COPD, Hypothyroidism, other | Number/ % asthma and COPD patients who receive control review (spirometry or clinical) in last year (Target = 80%) |
| Number of new diagnoses over a period of time | Number/% of asthmatics with acute exacerbations/ admissions in last year (Target = 20%) |
| Number/ % of exits per month: % defaulter, % dead (by primary diagnosis),  % self-transferred, % other | Number / % of DM patients/ hypertensives with mean BP <= 140/90 over last 12 months  (Target = 80%) |
|  | Number / % of DM patients with mean HbA1C < 8.0 % (or average FPG<150) in last 12  months (Target = 80%) |

Programmatic changes over time include introduction of: (1) a home visit team (2) a humanitarian liaison officer and (3) a formal MHPSS service. Technical changes introduced over time include: (1) task shifting to nurses of follow-up consultations (2) introduction of MSF-OCA NCD Guidelines and (3) implementation of spirometry. Contextual changes that occurred since programme inception include: (1) introduction of co- payments by the Jordanian government for Syrian refugees accessing MoH primary care services in November 2014 (2) increased recruitment of vulnerable Jordanians to the MSF NCD programme in the last quarter of 2015 and (3) closure of the MSF NCD programme to new patients from May to October 2016.

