| “Effectiveness”/ Quality of Care  What are the trends in clinical outcomes and quality indicators of the programme?  What are the perceived benefits/unintended consequences from a patient and provider perspective? | Clinical Outcomes | No./% patients with hypertension that have a most recent BP <= 140/90 6 and 12 months post enrolment and trend from baseline  Number / % of patients with diabetes that have a most recent BP <= 140/90 6 and 12 months post enrolment and trend from baseline  Number / % of patients with diabetes with last HbA1c < 8.0 %/ 7.0 % 6 and 12 months post enrolment and trend from baseline  Number/% with a reduction of >= 0.5 mmol/L in cholesterol level from baseline 6 and 12 months from enrolment  Number/% of patients with asthma / COPD free from exacerbations/ admissions in the previous 6 months  Number / % of patients who report decreased/quitting smoking within reporting period  Number / % of patients who report increased levels of exercise from baseline during reporting period  Trend recommended referrals to another facility for acute complications/specialist care, as a proportion of active cohort | Routine facility cohort data  Costing data (for incremental costing analysis)  2 Focus group with patients  Semi-structured interviews with approximately 12 clinic staff and 16 patients |
|  | Quality Indicators | Proportion of recommended referrals to other services that are appropriate as per guideline  Number/ % of active patients with CVD prescribed a statin during reporting period  Number/ % of patients with CVD prescribed aspirin during reporting period  Number/ % of patients with CVD prescribed at least one anti-hypertensive during reporting period  Number/% of patients with COPD/asthma with inhaler technique check documented  Number/ % of times when appropriate clinical action taken based on clinical or laboratory findings according to guideline (see Annexe 2d for detail)  Trend in defaulters as a proportion of active cohort during reporting period  Description of cohort deaths (patient characteristics) | Clinical audit  Participant observation  Routine health facility cohort data |
|  | Perceived Effectiveness | Patient and providers perspectives on effectiveness of programme components (clinical review, medications, HE, HLO, MHPSS, HV) | Key informant interviews  2 Focus groups with patients  Semi-structured interviews with 12 MSF/clinic staff and 16 patients |

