### 3.4.2 Cohort study main outcome measures

The principal **clinical outcome measures** for patients in the cohort are:

DM: HbA1c < 7 or 8%; proportion of patients meeting individualised target at last visit within the reporting period and trend from baseline

Hypertension: BP < 140/90 mmHg: proportion of patients at target at last visit within the reporting period and trend from baseline

Cardiovascular disease: change in total cholesterol level from baseline

Asthma / COPD: Free from exacerbations / admissions in last six months

The principal **quality of care outcome measures** are the following:

Number/ % of active patients with CVD prescribed a statin during reporting period

Number/ % of patients with CVD prescribed aspirin during reporting period

Number/ % of patients with CVD prescribed at least one anti-hypertensive during reporting period

Number/% of patients with COPD/asthma with inhaler technique check documented

Number/ % of times when appropriate clinical action taken based on clinical or laboratory findings according to guideline (see Annexe 2e for detail)

Description of trends and patient characteristics in programme defaulters and deaths

Proportion of recommended referrals to other services that are appropriate as per guideline

Death is defined as confirmed death reported by family or community member. A defaulter is defined as a patient who has not attended any NCD clinic appointments within the last 90 days, is not known to have died or moved out of the area, and has not been successfully contacted by phone on two occasions by the clinic registrar. The definition was changed in October 2016 to reflect the newly extended appointment interval for stable patients to: two consecutive missed appointments; not known to have died, moved out of the area, or become immobile and ineligible for home care; and has not been successfully contacted by phone on two occasions by the clinic registrar.

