### 3.4.3 Cohort data sources

The cohort will use retrospective routine facility data collected from files of patients admitted from the start of January 2015 to the end of December 2016. Data on costs for the economic analysis will be obtained from logistics supply, accounting and pharmacy records, and from time estimates obtained through observation and discussions with staff (see below for more details).

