### 3.4.5 Cohort data analysis

Cohort data from both clinics will be aggregated and will be analysed using RStudio v1.0.136 (RStudio, Boston, MA 02210, USA). Descriptive statistics will be used to describe the patient cohort, explore clinical outcomes and analyse trends in outcome measures from baseline. To attempt to account for programmatic changes that occurred since the intervention began, comparison will be made between patients who entered the programme during different periods. Analysis will include proportions and means, presented with 95% confidence intervals (95%CI). Differences in proportions will be measured using Pearson χ2 test while differences in means will be measured using two-sample t-tests, presented with p-values. Clinical outcomes will be compared using multiple linear regression to explore the effect on key clinical outcomes of age, gender, origin (Syrian or Jordanian), economic status, mobility, type and number of morbidities (including relevant, identified mental health co-morbidity), and number of medications/pill burden.

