# 6 Limitations

The study design does not allow us to ascertain clinical impact or effectiveness of the programme since we have not included a comparator group. In addition, the two-year time frame and cohort size involved in this evaluation mean that typical clinical endpoints used in the study of chronic conditions, such as all-cause mortality, fatal and non-fatal myocardial infarction, cannot be measured. It is well established that improvement in surrogate measures i.e. clinical or biochemical parameters such as blood pressure, cholesterol or HbA1c, represents a reduction in cardiovascular risk^[[1]](#footnote-1)^. If maintained, this would result in a reduction in morbidity and mortality. In addition, improvements in clinical parameters are assumed to be due to the intervention itself but may be as a result of other, indeterminate factors, such as a patient receiving NCD care and/or medications from another source concurrently. Insight will be gained regarding this latter potential bias through focus groups and semi-structured interviews.

While literacy rates are quite high among Syrians (92% for men; 81 % women), we recognise this could still lead to potential bias in the adherence survey and also that literacy rates will vary by sub-group (e.g. based on gender, age, socio-economic background). To try and reduce this bias, a data collector will administer the adherence questionnaire to patients with limited literacy (and this will be recorded on the questionnaire).

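### The entry-period comparison in 3.4.5 fixes no time point: on the last-visit outcome it confounds programme change with length of care, and entry period does not measure exposure to the added components

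*Protocol*

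**What the plan says.** Section 3.4.5 gives the cohort analysis one way of dealing with a programme that kept changing. Its purpose is put as "To attempt to account for programmatic changes that occurred since the intervention began". The method chosen for this is that a "comparison will be made between patients who entered the programme during different periods". Proportions are compared by Pearson chi-square and means by two-sample t-test, with both clinics pooled. The periods are not defined, and no outcome or time point is named. The regression in the same section includes origin, but not entry period, clinic, baseline value or time since enrolment.

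Two timings for the outcomes are on offer. Section 3.4.2 makes the principal hypertension outcome the "proportion of patients at target at last visit within the reporting period and trend from baseline", and treats HbA1c in the same way; the reporting period is never defined. Table 2 has the same indicators at fixed times, for example "most recent BP <= 140/90 6 and 12 months post enrolment and trend from baseline".

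On dates, section 3.4.3 uses "files of patients admitted from the start of January 2015 to the end of December 2016", which bounds admission only. The executive summary describes the cohort as "using patient records from January 2015 to December 2016", which bounds the records, and the limitations section refers to "the two-year time frame and cohort size involved in this evaluation". Section 1.1.4 reports "closure of the MSF NCD programme to new patients from May to October 2016". Section 1.1.5 dates the home visit service and the liaison officer to August 2015 and the mental health service to April 2016.

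**The concern.** Two separate faults follow from grouping patients by entry date.

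First, if the outcome is read at the last visit and follow-up ends on one calendar date for everyone, early entrants have had much longer treatment than late ones. Cohort entry needs two visits and has no minimum duration (3.4.1), and prescriptions run for at most a month (1.1.2), so very recent entrants can qualify. If control improves with time in care, late entrants look worse without any programme change.

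Second, the changes arrived on calendar dates in a running service. An eligible patient who enrolled early and stayed could use each component once it began. Early against late entry is therefore not unexposed against exposed.

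At stake is the reading of the trends that the evaluation reports: a p-value between entry periods could be taken as a sign that the programme declined, or that an addition did not help.

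**Working it through.** The protocol gives no sample size, effect size or error rate for this comparison, so there is no figure of its own to reproduce. The check is date arithmetic followed by an illustration.

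**Step 1: time from entry to 31 December 2016.** Inputs: admission from 1 January 2015 to 31 December 2016 (3.4.3), intake closed May to October 2016 (1.1.4), records to December 2016 (executive summary). Months = days / 30.4375; means assume uniform entry.

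| Entry period | Months to cut (range) | Mean |
|---|---|---|
| Jan-Jul 2015 | 17.1-24.0 | 20.5 |
| Aug 2015-Mar 2016 | 9.0-17.0 | 13.0 |
| Apr 2016 | 8.0-9.0 | 8.5 |
| Nov-Dec 2016 | 0-2.0 | 1.0 |

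A later cut adds the same time to every row, so the difference of about 22 months in maximum follow-up between first and last entrants stays. With a cut at 28 February 2018, the end of the study period in the key data table, the maxima become 37.9 and 15.9 months.

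**Step 2: exposure.** At 31 December 2016 a January 2015 entrant still in care has had 17.0 months since the home visit and liaison services began and 9.0 months since the mental health service began. A November-December 2016 entrant has at most 2.0 months of either. The group that entered before the mental health service can thus have had more access to it than the group that entered after. Of 547 days open to entry, 91 (17%) fall after that service began: 30 in April 2016 and 61 in November-December.

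**Step 3: illustration with no programme effect.** Assumed curve, not from the protocol: p(t) = 0.40 + 0.25 × (1 − exp(−t/τ)), with τ = 2, 4 or 6 months. Its mean over follow-up from a to b months is 0.65 − 0.25τ × [exp(−a/τ) − exp(−b/τ)] / (b − a). For τ = 4 over 0.5 to 2 months: 0.65 − 1 × (0.8825 − 0.6065) / 1.5 = 0.466.

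*Extreme contrast*, 18-24 months (first half of 2015) against 0.5-2 months (November-December 2016), cut December 2016:

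| τ | Early | Late | Gap (points) |
|---|---|---|---|
| 2 | 0.650 | 0.513 | 14 |
| 4 | 0.649 | 0.466 | 18 |
| 6 | 0.642 | 0.446 | 20 |

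*Other contrasts with the same curve:*

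| Contrast | τ = 2 | τ = 4 | τ = 6 |
|---|---|---|---|
| Entry before / from April 2016, December 2016 cut (late group weighted 30:61 days) | 9.3 | 12.6 | 13.6 |
| Jan-Jul 2015 / Aug 2015-Mar 2016, December 2016 cut | 0.1 | 1.0 | 2.2 |
| Extreme contrast, March 2017 cut (+3 months) | 3.1 | 8.6 | 11.9 |
| Extreme contrast, February 2018 cut (+14 months) | 0.0 | 0.6 | 1.9 |

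A second set of assumed curves (start 40% or 50%, plateau 70%, τ 3 to 12 months) gives 15-25 points between January-July 2015 and November-December 2016 entrants with a December 2016 cut.

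**Step 4: fixed time point.** Read at 6 months after enrolment, the artificial gap in this illustration is zero by construction. The exposure problem in step 2 is untouched.

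**The case against.** The strongest reply is that section 3.4.5 does not tie the entry-period comparison to the last visit, and that Table 2 already holds 6- and 12-month versions in which follow-up is aligned. That stands. A reader might infer that the protocol commits itself to the biased version; it does not. What it does is offer two timings and leave the comparison without one.

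A reader might also infer that the comparison is meant to judge the effect of each change. The text says only that it attempts to account for them, and sections 2, 3.4 and 6 disclaim any assessment of effectiveness. Nor is it the plan's only response to an evolving programme: costs are examined by component, and interviews ask about each one. It is the only response within the cohort analysis.

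The size is also conditional. A December 2016 cut is supported by the executive summary, but section 3.4.3 bounds admission alone. The periods are undefined, so 24 against under 2 months is the extreme contrast and not necessarily the one that will be made. HbA1c is repeated every three months, so under that cut the latest entrants would have no scheduled repeat, and the curve suits blood pressure better.

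Finally, it would be too strong to say that early entrants were exposed to everything. Home visits serve frail or immobile patients near the clinics, the liaison and mental health services work by referral, and patients who defaulted or died may have left before a change.

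None of this supplies the missing time point or turns entry date into exposure. A SAP could add the detail, but the grouping variable and the unadjusted tests are already fixed here.

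**Conclusion.** The point holds in a conditional form. Sections 3.4.2 and Table 2 time the same outcomes differently, and 3.4.5 does not choose between them. If the last visit is used with records to December 2016, entry period is tied to length of care, with maxima of 24 against under 2 months, and late entrants can look worse with no programme change. The artificial gap is 14-20 points at the extreme contrast, 9-14 for a split at April 2016, and about 0-2 for early splits or a February 2018 cut. These sizes rest on an assumed rise from 40% to 65% control with a time constant of 2 to 6 months; the direction needs only that control improves with time in care.

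The exposure fault depends on neither the data cut nor the choice of outcome: entry period does not separate patients who had access to a component from those who did not. The documents do not support the stronger conclusion that the planned results will necessarily be wrong by these amounts.

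**What to change.** In section 3.4.5:

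- State the data cut and the entry periods, and define the reporting period used in 3.4.2.
- Compare entry periods on Table 2's 6-month outcome, and the 12-month outcome where reached, only in patients enrolled at least that long before the cut. Adjust for baseline value, clinic and origin.
- Keep the last-visit outcome as a description of the caseload, reported with its median follow-up.
- If programme changes are examined, use the dated visit values with months since enrolment and calendar period as separate terms, or recorded use of each component. Report this as descriptive: calendar terms show when a component was available, only some patients used each one, and other changes, such as nurse follow-up and the new guideline, overlapped.

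The cost is analysis time; the visit-level records are already collected. The downside is lost late entrants. With a December 2016 cut, November-December 2016 entrants have no 6-month value, and no one who entered once the mental health service began in April 2016 has a 12-month value, since their maximum is 9.0 months.

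### Section 3.4.5 names only independent-sample tests and does not limit them to comparisons between different patients, although change from baseline in the same patients is part of the principal outcomes

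*Protocol*

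**What the plan says.** Section 3.4.2 lists the principal clinical outcomes. For diabetes it is the "proportion of patients meeting individualised target at last visit within the reporting period and trend from baseline"; for hypertension, the "proportion of patients at target at last visit within the reporting period and trend from baseline"; for cardiovascular disease, the "change in total cholesterol level from baseline". Table 2 repeats the idea at fixed times, for example "most recent BP <= 140/90 6 and 12 months post enrolment and trend from baseline".

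Section 3.4.5 gives the analysis in this order:

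- Descriptive statistics will be used to "explore clinical outcomes and analyse trends in outcome measures from baseline".
- Patients who joined the programme in different periods will be compared.
- Proportions and means will carry 95% confidence intervals.
- "Differences in proportions will be measured using Pearson χ2 test", while "differences in means will be measured using two-sample t-tests, presented with p-values".
- Multiple linear regression on patient characteristics follows.

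The sentence naming the two tests does not say which comparison it serves. No paired t-test, McNemar test, mixed model or GEE appears in the protocol. Nor does the protocol say that a baseline figure will be computed only on patients who also have the corresponding follow-up value.

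**The concern.** A trend or change from baseline compares a patient with himself or herself. Pearson chi-square and the two-sample t-test assume that the two groups contain different people. Ignoring the within-patient correlation misstates the uncertainty of the change, so a real change in a smaller disease group could be reported as compatible with none.

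A second issue sits beside this one and is separate from the choice of test. If baseline is summarised over everyone and follow-up over those still attending, the difference contains both true change and a change in who is being measured. If poorly controlled patients leave more often, the programme appears to improve control even when no patient's control changes. Before-after trends are a main part of how the protocol examines effectiveness, which it defines as quality of care (Section 2), so both issues touch the central clinical description.

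**Working it through.** **Inputs.** The cohort analysis states no sample size, power or significance level, so there is no figure of the plan's own to reproduce. The protocol gives no within-patient correlation, standard deviation, control rate or retention rate. All values below are assumptions, shown over a range.

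**1. Effect of ignoring pairing on a mean change.** With n patients, the same standard deviation σ at both times and within-patient correlation ρ:

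- SE unpaired = σ√(2/n)
- SE paired = σ√(2(1−ρ)/n)
- ratio = 1/√(1−ρ)
- true size of a nominal 5% unpaired test = 2[1 − Φ(1.96/√(1−ρ))]

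| ρ (assumed) | SE ratio | SE and interval too wide by | True size |
| --- | --- | --- | --- |
| 0.2 | 1.118 | 12% | 2.8% |
| 0.3 | 1.195 | 20% | 1.9% |
| 0.5 | 1.414 | 41% | 0.6% |
| 0.7 | 1.826 | 83% | 0.035% |
| 0.8 | 2.236 | 124% | 0.001% |

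The error always runs in the conservative direction when ρ is positive.

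**2. The same for a proportion at target.** Paired variance = unpaired variance − 2φ√(p₀q₀p₁q₁)/n, where φ is the within-patient correlation of the binary outcome. With assumed n = 1,000 and 50% rising to 55%, the 95% half-width is 4.4 points unpaired. Paired, it is 3.9, 3.4 and 2.8 points for φ = 0.2, 0.4 and 0.6.

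**3. Consequence for power.** Assume SD 1.8 HbA1c points, true change 0.25, ρ = 0.5.

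- n = 300: SE unpaired = 1.8√(2/300) = 0.147; SE paired = 0.104. The unpaired test rejects when the observed change exceeds 1.96 × 0.147 = 0.288, so its power is Φ((0.25 − 0.288)/0.104) = 36%. Paired power is Φ(0.25/0.104 − 1.96) = 67%.
- n = 1,000: the same steps give about 95% unpaired and 99% paired.

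The loss therefore matters in smaller groups and nearly vanishes in large ones. The protocol does not say how many diabetic patients there are.

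**4. Different patients at the two times.** Let a share p be controlled at baseline, let no patient change, and let retention be r_c in controlled and r_u in uncontrolled patients. The apparent gain is p·r_c/[p·r_c + (1−p)·r_u] − p. For p = 50%:

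- retention 80% v 70%: 0.40/0.75 = 53.3%, a gain of 3.3 points
- retention 80% v 60%: 0.40/0.70 = 57.1%, a gain of 7.1 points
- retention 90% v 60%: 0.45/0.75 = 60.0%, a gain of 10.0 points

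The gain is zero when retention is equal, or when each patient is compared with his or her own baseline.

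**5. Can the two patient sets differ under this protocol?** Yes.

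- Section 3.4.1 asks only for two recorded visits.
- Section 1.1.2 has HbA1c repeated every 3 months in diabetic patients and the cholesterol profile once a year, with prescriptions renewed at most monthly. A patient can qualify for the cohort without a repeat laboratory value.
- Admissions run to the end of December 2016 (Section 3.4.3). If records also end then, as the Executive Summary suggests, patients enrolled during 2016 cannot supply a full 12-month value.
- Defaulters and deaths are described as a separate outcome (Section 3.4.2), without a link to the baseline comparison. The limitations in Section 6 do not mention loss to follow-up.

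**The case against.** A reader might infer that the protocol assigns these two tests to change from baseline and that the central results will therefore be wrong. The text does not support that. Section 3.4.5 gives trends from baseline to descriptive statistics. The tests come shortly after the entry-period comparison, which is between different patients and for which they are valid. The Executive Summary also mentions logistic regression for outcome trends, although it names no within-patient term. This objection stands: the fault is an unrestricted sentence that allows the wrong use, not an explicit instruction to misuse the tests.

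Three further objections also stand.

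- The diabetes and hypertension measures begin with a single proportion at the last visit, whose interval needs no pairing.
- The cholesterol change, and the Table 2 indicator of a reduction of at least 0.5 mmol/L, already require both of a patient's values, so unequal patient sets cannot arise there.
- The protocol disclaims a formal assessment of effectiveness (Sections 2, 3.4 and 6), and no stated hypothesis depends on a before-after p-value.

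It can also be said that naming a paired test is a matter for a statistical analysis plan. That carries less weight here. The protocol does name tests, in general terms, and the ones it names do not suit part of its principal outcomes.

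**Conclusion.** The point holds as a should-fix. Trend or change from baseline in the same patients is part of the principal outcomes, and the only two-group tests named assume independent samples. If they are used for that change, its interval is too wide and its p-value too large: by 20%, 41% and 83% in standard error at assumed correlations of 0.3, 0.5 and 0.7. Confidence intervals for each separate mean or proportion are unaffected, and so is the entry-period comparison.

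It would be wrong to infer that the tests themselves produce false improvement. The unpaired error is conservative. An apparent gain from dropout arises only if baseline and follow-up are computed on different patients. The protocol does not propose this, but it does not exclude it either. The exposure is clearest for the 6- and 12-month trends, at about 3 to 10 points under the assumed retention rates. It is smaller for last-visit measures, because two visits are required. All sizes rest on assumed correlation, standard deviation, effect, sample size and retention.

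**What to change.** In Section 3.4.5:

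1. State that Pearson chi-square and two-sample t-tests apply only to comparisons between different patients, such as entry periods.
2. For change from baseline, use patients who have both values. Report the mean within-patient change (paired t-test) or the paired change in proportion (McNemar), each with a 95% confidence interval. Alternatively, fit a mixed or GEE model with patient-level clustering.
3. For each time point, give the number of patients with and without the follow-up value, and their baseline values side by side. Note that pairing removes the artefact of comparing different patient sets but not selection among those who stay.

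The cost is a few sentences and different R calls. No new data are needed.
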